## Abstract

**Background:**

An Early Warning Score is a clinical risk score based upon vital signs intended to aid recognition of patients in need of urgent medical attention. The use of an escalation of care policy based upon an Early Warning Score is mandated as the standard of practice in British hospitals. Electronic systems for recording vital sign observations and Early Warning Score calculation offer theoretical benefits over paper-based systems. However, the evidence for their clinical benefit is limited. Previous studies have shown inconsistent results. The majority have employed a “before and after” study design, which may be strongly confounded by simultaneously occurring events. This study aims to examine how the implementation of an electronic early warning score system, System for Notification and Documentation (SEND), affects the recognition of clinical deterioration occurring in hospitalised adult patients.

**Methods:**

This study is a non-randomised stepped wedge evaluation carried out across the four hospitals of the Oxford University Hospitals NHS Trust, comparing charting on paper and charting using SEND. We assume that more frequent monitoring of acutely ill patients is associated with better recognition of patient deterioration.

The primary outcome measure is the time between a patient’s first observations set with an Early Warning Score above the alerting threshold and their subsequent set of observations. Secondary outcome measures are in-hospital mortality, cardiac arrest and Intensive Care admission rates, hospital length of stay and system usability measured using the System Usability Scale. We will also measure Intensive Care length of stay, Intensive Care mortality, Acute Physiology and Chronic Health Evaluation (APACHE) II acute physiology score on admission, to examine whether the introduction of SEND has any effect on Intensive Care-related outcomes.

**Discussion:**

The development of this protocol has been informed by guidance from the Agency for Healthcare Research and Quality (AHRQ) Health Information Technology Evaluation Toolkit and Delone and McLeans’s Model of Information System Success. Our chosen trial design, a stepped wedge study, is well suited to the study of a phased roll out. The choice of primary endpoint is challenging. We have selected the time from the first triggering observation set to the subsequent observation set. This has the benefit of being easy to measure on both paper and electronic charting and having a straightforward interpretation. We have collected qualitative measures of system quality via a user questionnaire and organisational descriptors to help readers understand the context in which SEND has been implemented.

**Electronic supplementary material:**

The online version of this article (doi:10.1186/s12911-016-0257-8) contains supplementary material, which is available to authorized users.

## Background

Worsening physiological observations have been repeatedly shown to precede adverse outcomes in the hospital patient population [1–3]. However, these physiological alterations may go unrecognised, resulting in treatment delay [4]. Delays in appropriate treatment are known to worsen outcomes in acutely ill patients [2, 5, 6].

The concept of an Early Warning Score (EWS) was developed to aid recognition of deteriorating patients and has been adopted internationally [7–9]. An EWS is a weighted scoring system based upon vital sign observations – heart rate, blood pressure, temperature, respiratory rate, oxygen saturation and conscious level. The higher the EWS, the more abnormal the patient’s vital signs. NICE recommends that an EWS should be accompanied by an institution-specific protocol which stipulates changes in monitoring frequency and clinical management based upon the score [6].

Despite their theoretical benefits, EWS systems have not consistently been shown to affect hospital length of stay or mortality [10, 11]. Previous work has suggested that EWS systems may be less effective than anticipated because, scores are incorrectly assigned to individual vital signs, EWS values are incorrectly calculated or the care is not escalated appropriately [12–14].

Electronic EWS systems have the potential to mitigate some of these flaws. An electronic EWS system can be designed to automatically assign correct scores to vital signs, compute the EWS and prompt appropriate action. Where included, a central dashboard displaying recent observations and summary scores may increase the oversight of junior colleagues, facilitating improvements in the standards of practice.

Studies of electronic EWS systems have shown inconsistent results [15–17]. Many have used “before and after” design methodologies, comparing data from periods several years apart, with little attempt to correct for confounding factors [18]. This study design is strongly discouraged by the Cochrane Effective Practice and Organisation of Care (EPOC) Group [19]. At present there is no robust evidence to support or refute the case for the introduction of electronic EWS systems.

This study has been designed to investigate the clinical effectiveness of an electronic EWS system, System for Electronic Notification and Documentation (SEND). SEND will be rolled out sequentially according to a stepped wedge design across wards within each of four hospital. This will allow comparison of the electronic system with the paper system taking into account confounding factors and controlling for the effect of time without some of the limitations of previous studies.

### System description

A full description of SEND has been published previously [20]. In common with the other electronic charting systems [17, 21, 22] it provides automatic calculation of the EWS, displays relevant advice from local Trust protocols and provides an overview of the EWS values of all patients in a clinical area.

Tablet computers used for data entry are mounted on the same stands as the physiological monitors used to measure patient vital signs (Fig. 1). This design is intended to minimise barriers to timely data entry and facilitate viewing of current and historical observations at the point of care using a graphical format that is familiar to clinical staff (Fig. 2). In order to minimise errors from misattribution of data, patients are identified by scanning their hospital wristband barcodes.

**Fig. 1 Fig1:**
[figure not shown]
The SEND data entry hardware. Observation roll stand with equipment for taking observations, barcode scanner and tablet computer

**Fig. 2 Fig2:**
[figure not shown]
The chart viewing screen

### SEND Implementation Plan

SEND will be used for the recording of routine observations on all adult wards and day units except for obstetrics wards and intensive care units (ICUs). A different EWS is used on obstetric wards and the ICUs already have an electronic charting system integrated into their patient record system.

Deployment on each ward is a five week procedure, consisting of 3 weeks of preparation followed by two weeks of enhanced support following the date the system is activated on the ward. (Fig. 3) During the enhanced support weeks project staff are available on the ward to identify problems and offer additional training to users. In some cases it will be necessary to roll out groups of related wards simultaneously to ensure patient care is not compromised. Roll-out is planned to commence on a new ward (or group of wards) every fortnight. However, it is anticipated that practical difficulties may prevent this occurring in all cases. The sequence of ward roll-out is determined by pragmatic and patient safety considerations rather than being randomised.

**Fig. 3 Fig3:**
[figure not shown]
The implementation process for each ward

As part of the implementation process ward managers are given access to a real-time audit report showing observation recording compliance at a ward level against Trust standards. This can be accessed at any time through the SEND application. A sample report is shown in the supplementary information. [Additional file 1].

## Methods

The study will use a non-randomised stepped wedge design carried out across the four hospitals of the Oxford University Hospitals (OUH) NHS Trust. A stepped wedge cluster design [23, 24] was chosen as it addresses the problem inherent in studying changes in process improvement [19].

A number of issues mitigate against the use of a randomised controlled trial. SEND must be simultaneously implemented for all patients within a ward. It is not removed once implemented in a study ward. Roll out must proceed sequentially across all wards. The order of ward roll out is dictated by operation factors and patient safety considerations therefore it is not be possible to randomise order in which the system is implemented in the study wards.

SEND will be implemented in all study wards in a stepwise fashion. Each time point at which a new study ward receives SEND marks the beginning of a new step. All study wards will have received SEND by the time point of the final step. The outcomes are measured in all study wards in each step. Observation recording practice will be assessed before and after the start of each step. The effect of time can be investigated and controlled for in the statistical analysis.

### Setting

The four hospitals include a district general hospital, Horton General Hospital, and three teaching hospitals (John Radcliffe Hospital, Churchill Hospital and Nuffield Orthopaedic Centre). The effects of implementation will only be studied on general wards (Level 0 and Level 1 wards as defined by the Intensive Care Society guidelines [25]). Day units, investigational units and higher dependency areas will not be studied. The Emergency Department and the Acute Medical Unit will also be excluded from study, as the manner in which these areas operate is substantially different from the remainder of hospital wards. The wards included in the study are hereafter referred to as ‘study wards’.

### Aim

The aim of this study is to determine whether introduction of SEND affects nursing recognition and response to signs of patient clinical deterioration.

### Hypothesis

The OUH NHS Trust has implemented the Centile-based Early Warning Score (CEWS) which defines at-risk patients as having a CEWS score of 3 or more [26]. Trust protocols mandate that a repeat observation of the vital signs should be performed within 1 h whenever a patient is at risk. Local audit suggests that these standards are not consistently met. Similar problems have been observed in other institutions [8, 22].

It is anticipated that SEND may affect the adherence to local policies on the frequency of observation recording for patients. As a result the observation frequency may change. A number of system features have the potential to contribute to this change. Integration of a tablet with vital signs monitors has previously been shown to reduce the time taken to record observations [27]. Preliminary data suggest that charting using SEND is faster than on paper. Lowering staff workload may improve observation frequency. SEND provides on-screen prompts and auditing of performance. Such measures have been shown to improve the frequency of observation recording [22]. However, staff are used to paper-based systems, which are readily accessible. Poor implementation of electronic vital signs systems has previously resulted in decreased charting rates [28].

Frequent patient observation is necessary but not sufficient to affect clinical outcome measures. The translation of improved management of deteriorating patients by nursing staff to better patient outcomes is dependent on the response of doctors as well as organisational facilities and processes – the “effector arm”. The implementation of SEND does not contain any measures designed to specifically improve the effector arm, therefore use of measures such as mortality or length of stay as the primary endpoint would not be suitable for assessing whether SEND improves nursing management. Nevertheless, these are clinically important measures and will be reported as secondary endpoints.

### Inclusion and exclusion criteria

The study period will commence two weeks prior to the roll out of SEND on the first ward in the initial hospital and finish three months after the roll out of SEND on the final ward in the final hospital. During this period all patients over the age of 16 years admitted to a study ward will be included, unless Trust protocol dictates that their observations should be recorded on a maternity observation chart. Admission episodes in which vital signs are charted on both paper and electronic systems during a single admission will also be excluded.

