### Primary outcome measure

A patient is defined as being at risk of deterioration if they have a ‘triggering observation set’, one where the EWS ≥ 3. These patients should be observed at least hourly until the EWS falls below 3. The primary outcome measure is the time between a patient’s first triggering observations set and their subsequent set of observations. A shorter interval between observations is taken to represent improved response to potential deterioration.

To address potential confounding by patient length of ward stay, a triggering observation set will only be included in our analysis if it occurs within 48 h of admission to a study ward. If a patient has triggering observation sets on multiple study wards during the same admission episode only the first triggering set will be included in the analysis.

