#### Delayed Effect of intervention

It is possible that the effect of the intervention may increase as staff become more familiar with this system. Therefore the peak effect may be delayed for some weeks after roll out. This will reduce the power of the study. Additional follow-up time is a recognised method of compensating for this issue [33]. We will continue data collection for a further 3 months after completion of the last ward roll out at each site. Additional analyses will investigate whether the treatment effect changes with time from implementation of SEND.

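### Excluding episodes charted on both systems cuts short the paper-side length of stay at each ward's switch, so SEND appears to lengthen stay even with no true effect

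*Protocol article*

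**What the plan says.** The exclusion sits in the general eligibility section (Inclusion and exclusion criteria), so it governs every endpoint: "Admission episodes in which vital signs are charted on both paper and electronic systems during a single admission will also be excluded".

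Other parts of the protocol article determine how it acts:

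- **One-way switch.** Of SEND, the Methods say "It is not removed once implemented in a study ward".
- **Timing.** From the SEND Implementation Plan: "Roll-out is planned to commence on a new ward (or group of wards) every fortnight". From the inclusion criteria: "The study period will commence two weeks prior to the roll out of SEND on the first ward in the initial hospital". From Delayed Effect of intervention: "We will continue data collection for a further 3 months after completion of the last ward roll out at each site".
- **Endpoint.** Length of stay is a secondary endpoint. It comes from the hospital Patient Administration System (PAS), and secondary endpoints are reported for each period-ward combination.
- **Safeguard.** The one rule aimed at stay belongs to the primary outcome: "a triggering observation set will only be included in our analysis if it occurs within 48 h of admission to a study ward".
- **Other areas.** "SEND will be used for the recording of routine observations on all adult wards and day units", apart from obstetrics and intensive care. Yet "The Emergency Department and the Acute Medical Unit will also be excluded from study".

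The section on compensation for potential biases does not mention the exclusion.

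**The concern.** Whether an episode touches both systems is known only after admission, and it depends on how long the patient stays. Because the switch runs only from paper to SEND, an episode spent on one ward can be mixed only if it began on paper. The rule therefore removes long stays from the paper side near each activation and none from the SEND side.

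Adjustment for ward and step does not cure this. The loss is tied to each ward's own activation date. In the same calendar step, wards far from their switch lose almost nobody and wards already live lose nobody. The selection therefore changes together with the SEND indicator itself. Staffing and case-mix covariates do not restore the missing long stays.

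At stake is a published finding that SEND prolongs hospital stay, produced by the eligibility rule alone.

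**Working it through.** The article gives no length-of-stay figure and no expected number of excluded episodes, so there is no stated value to reproduce. Its power figure concerns the primary outcome and is not used here.

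**Inputs from the article:** fortnightly steps; a two-week paper run-in; a one-way switch; about three months of follow-up after the last ward.

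**Assumptions:** exponential stay with mean m; 12 wards switching one per fortnight; even admissions; no transfers; no SEND effect.

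**Step 1: the last paper fortnight.** Let T be the days from admission to activation. The patient is kept with probability 1 − e^(−T/m). Averaged over T from 0 to 14:

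share kept = 1 − (m/14)(1 − e^(−14/m))

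mean stay of those kept = [m − (m²/14)(2 − (2 + 14/m)e^(−14/m))] / share kept

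For m = 7:

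- share kept = 1 − 0.5 × (1 − 0.1353) = 0.568, so 43% are excluded
- mean stay kept = (7 − 3.5 × 1.4587) / 0.568 = 1.895 / 0.568 = 3.34 days, against a true 7

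**Step 2: earlier fortnights.** Averaging the same quantities over T from 14 to 28 gives 94% kept, with mean stay 5.8 days. The distortion is concentrated near the switch.

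**Step 3: effect on the comparison.** I placed these expected cell means in the 12-ward layout, with SEND cells at m, and fitted ward + period + SEND by least squares. The layout has 13 fortnights (run-in plus 12 steps), or 19 with three months of follow-up.

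| Assumed mean stay (days) | Excluded, last paper fortnight | Mean stay of those kept (days) | False SEND effect (days), equal cell weights: 13 / 19 fortnights | Same, cells weighted by patients kept |
|---|---|---|---|---|
| 3 | 21% | 2.2 | +0.34 / +0.27 | +0.29 / +0.23 |
| 5 | 34% | 2.9 | +1.02 / +0.80 | +0.80 / +0.62 |
| 7 | 43% | 3.3 | +2.02 / +1.60 | +1.52 / +1.19 |
| 10 | 54% | 3.7 | +4.00 / +3.20 | +2.97 / +2.34 |

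**Step 4: a different stay distribution.** A patient-level simulation used lognormal stays with means of 4, 6 and 8 days (SD 5, 8, 10), 10 wards, 2 admissions per ward per day, no SEND effect and 40 replicates per scenario.

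- Without transfers, 5.1%, 7.6% and 10.0% of all paper episodes were dropped, and no SEND episodes.
- In the fortnight before a switch, 26%, 36% and 45% of paper admissions were dropped.
- The false effect, adjusted for ward and step, was +0.7, +1.4 and +2.2 days. It was nominally significant in 75% to 98% of replicates.

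**Step 5: adding transfers.** At mean stay 6 days, with 6, 10 or 20 wards and two assumed transfer rates, the false effect was +0.7 to +1.6 days. Excluded episodes that involved a transfer numbered 67 paper to 38 SEND, 126 to 77, 29 to 13 and 233 to 172, a ratio of about 1.4 to 2.2.

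**Step 6: without the exclusion.** In the same simulations, keeping every episode and classifying it by the system at admission gave an estimated effect between −0.08 and +0.16 days, that is, about zero.

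**The case against.** The strongest reply is about scope. The harm shown is to one secondary endpoint, which the authors themselves regard as subject to many outside influences and implausible as a direct effect of a charting system. The article fixes no model for it, and the number of days rests on assumed stays and ward counts. All of this is fair and limits how the size may be stated. It does not remove the bias, since reporting by period-ward cell would show the same jump with no model fitted.

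Some stronger readings are tempting but not supported:

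- **Transferred patients are lost mainly from the paper side, as long stays are.** A move from a SEND ward to a paper ward is dropped too, so the imbalance is moderate. For the Acute Medical Unit, which would receive SEND although it is not a study ward, the side that loses patients depends on roll-out order. The article does not give that order. It also allows related wards to go live together, which would reduce mixed transfers.
- **Every paper patient who reaches intensive care is excluded, because those units already chart electronically.** The abstract defines the comparison as paper against SEND, and the Statistics section plans an intensive care admission probability for each period-ward cell. Under this reading that probability would be zero in every paper cell, which cannot be intended. One clarifying word settles it.
- **Mortality, intensive care admission and the primary outcome are biased.** A changed case mix is possible, but no size has been shown. For the primary outcome, the 48 h trigger window and the 14 h follow-up leave later stay little room to act except through case mix, and patient-level covariates are planned.

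**Conclusion.** The concern holds for length of stay. Read with the one-way switch, the exclusion selects paper-side episodes on their duration at each ward's own activation date, and nothing else in the article corrects this. The truncation makes SEND appear to lengthen stay, and that direction held in every scenario tried.

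The size is illustrative only: about +0.3 to +4 days for assumed mean stays of 3 to 10 days without transfers, somewhat less if cells are weighted by patients kept, and +0.7 to +1.6 days at a mean of 6 days with transfers. It depends on stay distribution, ward count, transfer rate and roll-out order, none of which the article supplies. Effects on mortality, intensive care admission and the primary cohort's case mix remain possible but unquantified.

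**What to change.** 1. **Secondary endpoints.** Do not apply the exclusion. Keep every episode and classify it by the charting system live on the first study ward at admission to it. Length of stay and hospital mortality already come from PAS, so no new outcome source is needed.
2. **Primary outcome.** Preferably classify by the system live on the ward at the triggering set, and censor at activation if that falls within the following 14 h. If the exclusion is kept here, report the number excluded by system and step.
3. **Wording.** State that electronic charting means SEND.
4. **Sensitivity analysis only.** Admissions in a fixed window before activation may be dropped whatever their stay. A 14-day window would remove the entire paper baseline of the first ward in the initial hospital, because the run-in is two weeks; the plan should say so.

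**Cost.** Episodes that straddle activation are partly exposed to SEND and dilute the secondary contrast somewhat. In the simulations without transfers they were 5% to 10% of paper episodes overall, but far more in a ward's last paper fortnight, which is the whole baseline of that first ward. Keeping mixed episodes in the primary analysis also adds paper-chart inspection for the single assessor, so the change is more than wording.

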### Primary outcome measure

A patient is defined as being at risk of deterioration if they have a ‘triggering observation set’, one where the EWS ≥ 3. These patients should be observed at least hourly until the EWS falls below 3. The primary outcome measure is the time between a patient’s first triggering observations set and their subsequent set of observations. A shorter interval between observations is taken to represent improved response to potential deterioration.

To address potential confounding by patient length of ward stay, a triggering observation set will only be included in our analysis if it occurs within 48 h of admission to a study ward. If a patient has triggering observation sets on multiple study wards during the same admission episode only the first triggering set will be included in the analysis.

